#### Recorded Variables and Source Data

Data will be collected directly from the questionnaires as the study progresses.

The information collected on the participants will include:

- Sociodemographic characteristics: Age, subjective age, sex, level of education, family situation, living conditions- Attendance and participation rates in the workshops- How they got to know about the Balance Workshops.- Individual Precariousness Index - Evaluation of the Deprivation and Inequalities of Health in Healthcare Centers (EPICES) Score: This assessment is made up of 11 questions that summarize the precarious situation of a person. A coefficient is assigned to each response, the sum of which gives the EPICES score which is continuous, and varies from zero (lack of precariousness) to 100 (maximum precariousness). The evaluation of this score has been relevant in detecting and quantifying precariousness. A value of 30 is considered as the Precariousness Threshold according to EPICES (45).- Level of quality of life: Questionnaire SF 36 is the generic questionnaire most often used in Medicine for the evaluation of the quality of life in general. It analyzes the physical, emotional and mental dimensions. The full version includes 36 questions (42, 43). A score for each dimension of the SF-36 is calculated, ranging from 0 to 100. Poor health, loss of function, and presence of pain were scored as low. Good health, absence of functional deficit and pain were scored as high.- Level of PA: IPAQ Questionnaire - E is a short version of the International Physical Activity Questionnaire for older adults. It was validated for the assessment of the level of PA in older adults and has seven questions that classify them at various levels of PA (44). Official IPAQ guidelines (46) are as follows: data are added “*within each item (i.e., vigorous intensity, moderate intensity, and walking) to estimate the total amount of time spent engaged in PA per week. Total weekly PA (MET-min week*−*1) was evaluated by adding the products of reported time for each item by a MET value, specific to each category of PA*” (46). “*MET values were assigned as projected for use with elderly adults: vigorous PA* = *5.3 METs, moderate PA* = *3.0 METs, and walking* = *2.5 METs*” (47).

## Statistical Analyses

### Number of Participants Required

In the Balance Workshops carried out by the “Caisses d'Assurance Retraite et de la Santé au Travail” (CARSAT) for the Loire and Rhône Regions in 2018, about 43% of those who registered went through the 12 sessions. Attendance was at 44% in the Loire Region and 42% in the Rhône Region. In our study, we hope to raise the attendance by about 20%, to get to 63% per group who go through the 12 sessions.

We compared two binomial proportions observed with:

$$\begin{array}{l} \text{π}1=0\text{.}43\text{ π}2=\;0\text{.}63\\ \text{α}=5\%\;Power1-\text{β}=\;0\text{.}9 \end{array}$$

The total number of participants required is 210 (with 105 for the Test Area and 105 for the Control Area).

### Description of Statistical Methods

The analyses will be carried out on the entire study population and also by groups, depending on whether they received the specific advertisement materials or not.

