## Materials and Methods

### Design and Setting (Study Status)

This quasi-experimental multicenter study is being conducted in three French Regions (Loire, Haute-Loire and Rhône). The quasi-experimental model was decided upon in view of testing causal hypotheses. It is envisaged that the program will be evaluated using a set of indicators that have been predefined.

The distribution of participants between the two groups (Test and Control) was based on the choice of the study designers. A Comparison group that is as close as possible to the Test group in terms of initial characteristics will allow us to identify the outcomes in the case where the Social Marketing campaign is not implemented. This method will bring proof as to whether the program will be the cause of the differences in outcomes between the Test and Comparison groups.

The Loire and Haute-Loire Regions were selected for the campaign to promote the Balance Workshops against falls in the older population. This was because of the presence of our partners for the implementation of the study. The Rhône Region was selected, not as a Test, but as the Control Area (Figure 1).

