### Recruitment in the Test Area

#### Selection

Individuals in the study areas who have seen the advertisement for the Balance Workshops and who fulfill the inclusion criteria will be eligible for the study. They will contact our partners (“Atouts Prévention” and “Association Régionale Santé Prévention sur les Territoires Auvergne” through the contact details provided alongside the advertisements) to register for the workshops organized by the French Federation of Physical Education and Voluntary Gymnastics (FFPEVG) at the local level.

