### Recruitment in the Control Area

#### Selection

In the same way as when registering people for the Balance Workshops, the FFPEVG of the Rhône will contact older people who meet the inclusion criteria.

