#### Inclusion Criteria

- Individuals aged 60 and over- Individuals living in the Loire, Haute-Loire or Rhône Regions of France- Individuals who do not have medical contraindications concerning participation in moderate PA- Individuals who have been fully informed about the study, including their rights over the data to be collected

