This study brings together a provider (the FFPEVG) and promoters (“Atout Prévention Rhône-Alpes” and ARSEPT Auvergne) which, in this case, are medico-social groups. Currently, the locations where the Balance Workshops take place belong neither to the provider nor to the promoters. To facilitate the setting up of these structures in our areas of intervention, we established collaborations with the City or Community Social Action Centers, which have rooms and gymnasia for such purposes. This joint collaboration between these various groups in these regions will provide a global solution to encourage older adults to move toward PA centered on balance.

Accessibility to the workshops, whether physical and/or financial, is an essential condition for the participation of older adults in these activities (52). This study will lead to the establishment of new workshops in all these areas of intervention, thus making the product more accessible to the target audience. Also, even if this Balance Workshop program is free in one region and costs very little in another, we wanted to offer incentives to be able to deepen our knowledge of their capacity or not to increase participation in our program.

The adaptation of the program to the needs and expectations of the older adults is also a condition that favors their participation (52). That is why we interviewed some of them to identify these issues and improve on our program. From the survey, we developed an intervention strategy that included appropriate communication with them (modification of communication tools and use of new media validated by them) and training of professionals with particular emphasis on the fears and expectations of their trainees.

We equally chose geographic segmentation. The Loire and Haute-Loire (Test) Regions will receive the marketing campaign, but not the Control Area (Rhône Region). These are neighboring Regions, so this introduces a bias in our study. Therefore, those who will run the program particularly in the Control Area, may have to make more efforts to increase participation in their workshops. Besides, local newspapers that are distinct for each area are being used to promote the workshops. However, these older adults move around; and so, some who live in the Control Area may become aware of the campaign and may want to participate in the workshops. There is therefore a risk of contamination of the study.

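### The protocol defines its comparison groups by area in one place and by receipt of advertising in another, and makes sight of the advertisement an entry condition in the Test Area only

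*Protocol article*

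**What the plan says.** **By area.** In Design and Setting (Study Status), "The distribution of participants between the two groups (Test and Control) was based on the choice of the study designers", and "The Rhône Region was selected, not as a Test, but as the Control Area". Number of Participants Required sizes the study at 105 for each area. The Discussion says the statistical evaluation will first compare the Test Area with the Control Area, and only in a second step relate quality of life and physical activity to exposure.

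**By exposure.** Description of Statistical Methods is the only place in the statistical section that defines groups. It analyses the whole population and also "by groups, depending on whether they received the specific advertisement materials or not". Univariate Analyses then compares participants according to their groups.

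**Entry.** Under Recruitment in the Test Area, Selection, people "who have seen the advertisement for the Balance Workshops and who fulfill the inclusion criteria will be eligible for the study". Under Recruitment in the Control Area, "the FFPEVG of the Rhône will contact older people who meet the inclusion criteria", with no mention of advertising. The Inclusion Criteria are based on residence ("Individuals living in the Loire, Haute-Loire or Rhône Regions of France") and list no exposure condition.

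**Contamination.** The Discussion expects that "some who live in the Control Area may become aware of the campaign and may want to participate in the workshops". No rate is given.

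**The concern.** The two group definitions do not give the same groups. A Rhône resident who saw the campaign is a control by area and exposed by receipt. The document does not say which definition governs attendance, the primary endpoint, so the choice could be made after the data are seen.

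The definitions also differ in quality. Area was fixed by the designers. Noticing and acting on an advertisement is a personal trait, plausibly linked to motivation, and motivation drives attendance. A contrast by receipt is therefore confounded at the individual level and can show a difference when the campaign does nothing.

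The Test Area entry condition brings the same trait into the area comparison, because it filters one arm and not the other. It also departs from the planning basis: the 43% completion figure describes people who registered for the 2018 workshops, not people who responded to an advertisement.

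**Working it through.** **The plan's own figure.** Inputs from Number of Participants Required: 0.43 against 0.63, alpha 5%, power 0.9. The pooled-variance formula is n = [z_a √(2p̄q̄) + z_b √(p1q1 + p2q2)]² / d², with p̄ = 0.53 and d = 0.20.
- One-sided: (1.645 × 0.7058 + 1.282 × 0.6915)² / 0.04 = 104.8, so 105 per group and 210 in total. This reproduces the plan.
- Two-sided: the same with 1.960 gives 128.8, so 129 per group and 258 in total. With 105 per group, two-sided power is 83%.

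The plan does not state sidedness; that is a separate matter. What counts here is that the calculation is for an area comparison.

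**Illustration of bias, with no campaign effect.** The document gives none of these rates, so all are assumptions:
- half of registrants in every area are keen;
- 80% of keen and 50% of other Test registrants saw the advertisement;
- 10% of keen and 5% of other Control registrants saw it;
- keen people complete 20 to 40 points more often;
- the arms are of equal size.

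Bias = (difference in keen share) × (20 to 40 points).

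*Advertisement condition enforced (every Test participant is exposed)*
- Test keen share: 0.40 / (0.40 + 0.25) = 0.615. Control: 0.50.
- Area gap: 0.115, giving 2.3 to 4.6 points.
- Exposed keen share: (0.615 + 0.05) / (1 + 0.075) = 0.619. Unexposed: 0.45 / 0.925 = 0.486.
- Exposure gap: 0.132, giving 2.6 to 5.3 points.

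*Advertisement condition not enforced*
- Keen share is 0.50 in both areas, so the area gap is 0.
- Exposed: (0.40 + 0.05) / (0.65 + 0.075) = 0.45 / 0.725 = 0.621. Unexposed: (0.10 + 0.45) / (0.35 + 0.925) = 0.55 / 1.275 = 0.431.
- Exposure gap: 0.189, giving 3.8 to 7.6 points.

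For scale, with 105 per group and a 43% base rate, a spurious 5-point difference raises the two-sided false-positive rate from 5% to about 11%.

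**Cost of analysing by area.** Suppose a share c of controls is exposed and responds fully, so the Control rate is 0.43 + 0.20c. At c = 10% the Control rate is 0.45 and the difference shrinks from 20 to 18 points. Two-sided power at 105 per group is 83% at c = 0, 75% at 10%, 65% at 20% and 53% at 30%.

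**The case against.** A reader might infer that the exposure comparison replaces the designed area comparison. The document does not support that. The Discussion puts Test Area against Control Area first and names exposure only in a second step, for quality of life and physical activity, not for attendance. The design and sample size are also by area.

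The wording in Description of Statistical Methods may itself be loose shorthand for area, since the Discussion speaks of whole regions receiving the campaign. Nothing says outright that an exposed Rhône resident will be reclassified. This is a fair reading, but it leaves the only definition in the statistical section at odds with the design.

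A reader might also infer that Test Area registrants who came through a friend or a doctor are certainly excluded. The condition appears only in the recruitment narrative. The formal criteria omit it, and the Abstract refers simply to people aged 60 and over who want to take part. Strict enforcement is not established, which is why the working shows both cases. The 3.8 to 7.6 point figure belongs only to the case without enforcement and cannot be combined with the claim that unexposed Test registrants are shut out.

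Finally, the correction does not make the arms alike: Control participants are still contacted by the provider. That stands as a limitation.

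**Conclusion.** The concern holds as an internal contradiction with a bias attached. The group definition in the statistical section conflicts with the design, the sample size and the first step in the Discussion. The Test Area entry condition conflicts with the Inclusion Criteria and has no counterpart in the Control Area.

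On the assumed rates, with no campaign effect, the spurious difference is about 2.3 to 4.6 points by area and 2.6 to 5.3 by exposure if the condition is enforced. It is 0 by area and 3.8 to 7.6 by exposure if it is not. In this example, then, the area contrast is free of bias only when the entry condition goes, and the exposure contrast is biased in both cases. The zero rests on equal keen shares among registrants in all areas, which the differing recruitment routes may not deliver. The sizes are illustrative; the conflict in the text does not depend on them.

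**What to change.** - **Description of Statistical Methods:** define the primary analysis groups by area, Loire and Haute-Loire against Rhône, regardless of reported exposure. Use area of residence, to match the Inclusion Criteria, so that a Rhône resident who attends a Test Area workshop is still analysed as a control.
- **Exposure:** use the item in Recorded Variables and Source Data on how participants learned of the workshops only for secondary analyses and to describe contamination.
- **Recruitment in the Test Area, Selection:** delete the condition of having seen the advertisement, so that eligibility follows the Inclusion Criteria in all three areas. If enrolment has already begun under that condition, report how it was applied.

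The cost is two wording changes and no new data. Contamination will dilute the area contrast, with two-sided power falling from about 83% to about 75% at an assumed 10% and further at higher rates. That dilution works against finding an effect, whereas self-selection can create a false one. The different recruitment route in the Control Area remains and should be reported as a limitation.

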#### Multivariate Analyses

Analysis of Variance (ANOVA), Generalized Linear Model (GLM), Mixed Model, analyses of multiple components to identify groups of individuals (the study of their profiles).

### Evaluation of the Social Marketing Benchmark Criteria

The Table 1 present the definition and the evaluation of each social marketing benchmark criteria.

**Table 1 T1:** Definition and evaluation of each social marketing benchmark criteria.

**Social marketing steps**	**Définition**	**Evaluation**
Behavioral objective	Defining a behavioral change objective for the intended target audience is fundamental, especially for evaluating the effectiveness of an implemented program	Statistical analysis about an increase or not of PA participation and level
Formative research	Understanding the target audience is based on conducting market research. Market research provides an in-depth understanding of the needs, desires, values and lifestyles of the target audience. The purpose of market research is to inform the planning, development and implementation of social marketing programs	We did this step 1 year before the beginning of the study and allow us to build the research protocol.
Segmentation	Segmenting means creating homogeneous groups of individuals with identifiable similarities. These similarities can be, for example, place of residence, age, lifestyle or health status	Subgroup analysis, particularly by age group, will allow us to know if this segmentation criterion was effective. The qualitative survey of participants in the study areas (control and intervention) will allow us to know if there was any pollution of the study due to the geographical proximity of our territories.
Exchange	To induce individuals to change their behavior, it seems important to provide them with something in exchange. R. Bagozzi assumes that the exchange between several social actors (e.g., the target audience and the promoters of a prevention programme) involves a transfer of tangible or intangible objects (36);	An intervention territory will offer the workshops for 0€ and another territory for 20€. The evaluation of the level of participation by adjusting this parameter will allow us to evaluate the relevance of the free workshops.
Marketing mix	Social marketers have therefore taken the “4Ps” concept from commercial marketing and adapted it (88, 89, 111): Product: the behavioral offer made to the target audience. The product involves intangible elements such as the adoption of an idea or behavior; Price: offering financial support mechanisms to address financial or psychological barriers to adopting the proposed behavior; Place: facilitating access to services or products that enable a change toward the proposed behavior; Promotion: promoting the behavior through the use of communication tools;	The qualitative survey among the participants of the study will allow us to know the relevance of the actions proposed for the four components of the marketing mix.
Competition	In social marketing, as in commercial marketing, practitioners need to be aware that there are sources of competition to the adoption of the proposed behavior. The main source of competition is the tendency of the target audience to maintain their current behavior, especially when that behavior involves an addiction (tobacco, alcohol, drugs, etc.).	The qualitative survey of participants will allow us to assess the influence of other physical activity providers on the decision to participate or not in the proposed program.
Evaluation	An assessment of the program is carried out	We will conduct a statistical evaluation as well as a qualitative survey

### Monitoring

No extra examinations or treatment besides traditional practices will be done; except the digitization of all findings for analysis. During analysis, data will be kept confidential and anonymous. No intervention will be done outside of normal practice. For participants, we do not forsee any unusual risk or specific constraint.

### Ethical Considerations

The “Crédit Agricole Loire/Haute-Loire” Foundation funded the study and the Jean Monnet University of Saint-Etienne reviewed it. The Ethics Committee of the University Teaching Hospital of Saint-Etienne approved and peer-reviewed the study on September 6th, 2019, under Reference Number: IRBN622019/CHUSTE.

Data collection will start in September 2020 and the planned end date for this activity is July 2021. Data analysis will take place in the summer of 2021 and the first results are expected to be published in late 2021.

All participants will receive information brochures, and give their oral informed consent (because of more difficulties in seeing and writing in older adults).

Approval for important protocol modifications will be sought from the Ethics Committee as the need may arise. There are no anticipated risks associated with participation in the study. Patients will be free to withdraw at any time. Data will be kept confidential and anonymized for the analyses.

### Access to Data

Accessibility to cleaned data to all Principal Investigators will be guaranteed. Project data sets will be kept on the LimeSurvey database created for the study, and the data sets will be accessed through a password. Project Principal Investigators will have unlimited access to their own site's data sets, but will need a permission to have access to other sites'data. In order to re-inforce the confidentiality, data shared with project team members will be blinded.

### Publication Policy

The authors will review all publications following the guidelines given below.

#### Data Analysis and Release of Results

The scientific integrity of the project requires that sites'data be pooled before analysis and reported as such. Presentations and publications from the project will be expected to protect the integrity of the major objective(s) of the study. Presented data should not break the blind prior to the release of the endpoint data.

#### Review Process

Each paper or abstract, as described below, must be submitted for review of its appropriateness and scientific merit prior to submission.

#### Primary Outcome Papers

The primary outcome papers are publications that present outcome data, as decided by authors.

#### Other Study Papers, Abstracts and Presentations

Within this category fall all studies except those designated as “Primary Outcome.” Authors should all approved a paper or abstract before submission.

In case of calls to contribution (papers, workshops, symposia, volumes, etc) in respect to related studies, authors may select other team members to bring in their contribution. If time permits, this call may be shared with all team members.

### Reproducible Research

Data sharing statement: No later than 3 years after the collection of the year-1 data, they will be deposited, coded and anonymous in an appropriate data archive for sharing purposes.

## Discussion

Our study will assess whether a Social Marketing approach is more effective in encouraging older adults to participate in Balance Workshops to prevent falls and to be diligent throughout the program. In 2017 in France, more than 76% of everyday accidents among people aged 65 and over were falls (48). Group physical activity offers exist in the country and are very often free. However, few older people participate in such programs. Strategies to increase PA levels, including improving balance, are therefore of particular importance.

Different methods are available for professionals to use to increase PA among older adults. social marketing is used extensively by health actors and researchers in several areas such as smoking prevention, promotion of healthy eating and physical activity (18–22). Prevention interventions, based on social marketing principles, have been successfully carried out in different (13–15) and age groups (38–40).

Our study used the classic and widely-cited Social Marketing benchmark criteria as defined by Andreasen (30) and Gallopel-Morvan et al. (28), including the evaluation as a major step in the process (a seventh criterion) (28). However, it is difficult to evaluate the efficiency of Social Marketing in promoting PA among seniors. Few strategies used so far did not apply all the seven benchmark criteria (49). Fujihira et al. (41) and Goethals et al. (49) have showed that as a program frequently uses the social marketing benchmark criteria defined by Andreasen, it becomes more and more effective at changing the behaviors of its target population. Other reviews (18, 19, 50) have used the same classification criteria as Andreasen and reported similar findings. Social Marketing may therefore be potentially efficient in promoting PA among seniors (49). Given its increased use in such initiatives (51), we aimed at confirming its effectiveness among older adults.

This study brings together a provider (the FFPEVG) and promoters (“Atout Prévention Rhône-Alpes” and ARSEPT Auvergne) which, in this case, are medico-social groups. Currently, the locations where the Balance Workshops take place belong neither to the provider nor to the promoters. To facilitate the setting up of these structures in our areas of intervention, we established collaborations with the City or Community Social Action Centers, which have rooms and gymnasia for such purposes. This joint collaboration between these various groups in these regions will provide a global solution to encourage older adults to move toward PA centered on balance.

Accessibility to the workshops, whether physical and/or financial, is an essential condition for the participation of older adults in these activities (52). This study will lead to the establishment of new workshops in all these areas of intervention, thus making the product more accessible to the target audience. Also, even if this Balance Workshop program is free in one region and costs very little in another, we wanted to offer incentives to be able to deepen our knowledge of their capacity or not to increase participation in our program.

The adaptation of the program to the needs and expectations of the older adults is also a condition that favors their participation (52). That is why we interviewed some of them to identify these issues and improve on our program. From the survey, we developed an intervention strategy that included appropriate communication with them (modification of communication tools and use of new media validated by them) and training of professionals with particular emphasis on the fears and expectations of their trainees.

We equally chose geographic segmentation. The Loire and Haute-Loire (Test) Regions will receive the marketing campaign, but not the Control Area (Rhône Region). These are neighboring Regions, so this introduces a bias in our study. Therefore, those who will run the program particularly in the Control Area, may have to make more efforts to increase participation in their workshops. Besides, local newspapers that are distinct for each area are being used to promote the workshops. However, these older adults move around; and so, some who live in the Control Area may become aware of the campaign and may want to participate in the workshops. There is therefore a risk of contamination of the study.

Finally, though this study focuses on the evaluation of the whole intervention, stepwise evaluations will have to be carried out. For a start, an evaluation of the effectiveness of the campaign will be undertaken through the collection of data on the intention to participate in the study and to attend the workshops. Alongside, an economic evaluation will have to be done to know the most cost-effective and appropriate method of communication through which to encourage older adults to commit themselves to the program. A statistical evaluation will also have to be conducted to first of all highlight whether or not the campaign is more effective in the Test Area than in the Control Area. Then, in a second step, it will assess the evolution of the quality of life with PA levels as a function of exposure to the campaign. Lastly, a qualitative evaluation of the campaign will need to be carried out on the older adults and also on the actors in the field. This study will therefore evaluate the effectiveness of this Social Marketing approach and, if positive, will maximize the probability of the measures applied to be more sustainably adopted in the community.

However, this quasi-experimental model has some limitations. Just like for any technique applied only at the end of a program, the method can be significantly hampered by the lack of baseline data. Since such methods are based on certain causal assumptions, conclusions on causality are less pertinent/persuasive than those resulting from a randomized controlled trial.

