Although this method has proven its worth in these other contexts, its use in getting older adults to take part in regular PA remains limited (41).

The main objective of this study is to determine whether associating a Social Marketing program would increase the attendance rate of people aged 60 and over in Group Balance Workshops.

The secondary objectives of this study are: (1) to increase the participation rate in the Balance Workshop sessions, (2) to increase the level of the quality of life of the participants, and (3) to increase the level of PA among the people participating in the study.

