#### Evaluation Criteria

The primary endpoint is the attendance rate of the participants in the Balance Workshop sessions for fall prevention. The secondary evaluation criteria are the number of calls received for a registration request, the evolution of the level of the quality of life using the SF 36 questionnaire (42, 43) and the evolution of the level of PA of the participants using the short version of the IPAQ questionnaire for older adults (44).

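### The Discussion anticipates extra organiser effort in the Control Area, which conflicts with that area's role as the usual-practice comparator; such effort is neither limited nor recorded

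*Protocol article*

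**What the plan says.** In Design and Setting, the comparison group "will allow us to identify the outcomes in the case where the Social Marketing campaign is not implemented". Under Recruitment in the Control Area, the Selection paragraph keeps recruitment there at ordinary practice: "In the same way as when registering people for the Balance Workshops, the FFPEVG of the Rhône will contact older people who meet the inclusion" (the sentence is cut here by one word). The planning rates in Number of Participants Required also come from ordinary practice, the 2018 workshops: "Attendance was at 44% in the Loire Region and 42% in the Rhône Region".

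The Discussion first says of the areas: "These are neighboring Regions, so this introduces a bias in our study". The next sentence is: "Therefore, those who will run the program particularly in the Control Area, may have to make more efforts to increase participation in their workshops". The paragraph closes by acknowledging a risk of contamination.

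Two quantities must be kept apart. Under Evaluation Criteria, "The primary endpoint is the attendance rate of the participants in the Balance Workshop sessions for fall prevention". The planning rate for it has registrants as denominator: "about 43% of those who registered went through the 12 sessions". The first secondary objective, in the Background, is a different one: "to increase the participation rate in the Balance Workshop sessions".

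**The concern.** The comparator cannot be both usual practice and usual practice plus extra effort prompted by the study. The article puts no limit on the extra effort, does not standardise it and provides no record of it. It is also not offered as a threat to be guarded against. It follows from the neighbouring-region bias as something organisers may need to do. It would not remove that bias, because spill-over of the campaign into the Rhône and extra effort in the Rhône are separate influences on the same arm.

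There is one Control region, and allocation was by the designers' choice. Anything specific to the Rhône is therefore already mixed with the absence of the campaign. Unrecorded organiser effort would add a further difference that no later analysis could separate from the campaign effect.

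**Working it through.** **1. Statements side by side**

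| Place | What it implies for Control |
|---|---|
| Design and Setting | No social marketing campaign |
| Recruitment in the Control Area, Selection | Provider contacts eligible people as it normally does |
| Number of Participants Required | Rate expected from 2018 practice (43% pooled, 42% Rhône) |
| Discussion | Organisers may step up efforts on participation because the regions adjoin |

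The first three agree. The fourth does not fit with them.

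**2. Would the planned checks reveal the effort?** The item on how each participant heard of the workshops (Recorded Variables) and the participant survey on spill-over (Table 1) record what participants knew, not what organisers did. The Discussion also foresees a qualitative evaluation that includes field actors, but its subject is the campaign. None of these is a record of Control Area effort.

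**3. Reproducing the plan's figure.** Inputs from Number of Participants Required: p1 = 0.43, p2 = 0.63, α = 5% (sidedness not stated), power 0.90, equal groups. With p̄ = (p1 + p2)/2 = 0.53:

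n per area = [z_α √(2p̄(1−p̄)) + z_β √(p1(1−p1) + p2(1−p2))]² / (p2 − p1)²

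The square roots are √0.4982 = 0.7058 and √(0.2451 + 0.2331) = 0.6915.

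- One-sided: (1.645 × 0.7058 + 1.2816 × 0.6915)² / 0.04 = 104.8, so 105 per area and 210 in total. This matches the plan.
- Two-sided (z = 1.960): 128.8, so 129 per area and 258 in total.

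The stated 210 therefore corresponds to a one-sided 5% test. Both versions are carried below.

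**4. Sensitivity of power to the Control rate.** Test is held at 63% with 105 per area:

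power = Φ{ [(p2 − p1)√105 − z_α √(2p̄(1−p̄))] / √(p1(1−p1) + p2(1−p2)) }

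For Control at 48%: p̄ = 0.555, the roots are 0.7028 and 0.6948, and 0.15 × √105 = 1.537. One-sided: (1.537 − 1.645 × 0.7028)/0.6948 = 0.548, and Φ(0.548) = 0.708.

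| Control rate (43% is the plan's; the others are assumed) | Contrast, points | Power, one-sided | Power, two-sided |
|---|---|---|---|
| 38% | 25 | 97.9% | 95.7% |
| 43% | 20 | 90.1% | 83.2% |
| 45% | 18 | 83.8% | 74.8% |
| 48% | 15 | 70.8% | 59.1% |
| 53% | 10 | 42.9% | 31.0% |

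The document gives no size for the effect of extra effort, so these are illustrations and not forecasts. A 5-point rise removes a quarter of the planned contrast (5/20).

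**5. Direction.** The Discussion sentence speaks of participation, while the primary endpoint is attendance among those taking part.

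- Reminders or closer follow-up of registrants raise the numerator. Control attendance rises and the contrast shrinks.
- Wider recruitment raises the denominator. Attendance may not change, or may fall if the added registrants are less committed. At 38% the contrast would be 25 points, overstating the campaign effect.
- Successful recruitment in Control narrows the contrast on the secondary participation objective directly.

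**The case against.** The strongest reply is that the sentence is a conditional remark in the Discussion. It can be read as the authors naming a possible reaction by Control organisers, while the operative Methods text keeps Rhône recruitment as usual and describes neither campaign nor gift card there. This stands. A reader might infer that the plan prescribes a second promotion in Control, or that Control already fails as a comparator. The text does not support either.

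A reader might also infer that Control was meant to be free of any promotion. It was not: it is defined by the absence of the social marketing campaign, and the provider's usual contact was always part of it.

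Third, a reader might infer a bias towards no effect. That holds only if the effort improves attendance, and the sentence does not say that it would. Its wording also does not confine the effort to Control, so placing the whole shift in Control, as the power table does, is a simplification.

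Fourth, the authors disclose the neighbouring-region bias and plan qualitative work on contamination. This is fair as to spill-over. It does not cover organiser effort, which is disclosed only as a consequence and is not recorded.

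Finally, an article may leave operational detail to a fuller protocol. That would excuse the missing log. It does not excuse statements within the article that disagree on what Control organisers may do.

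**Conclusion.** The point holds as a conflict to reconcile, at the level of should-fix. The Discussion sentence is at odds with the counterfactual role of the Control Area and with its usual-way recruitment. If organisers act on it, the primary area comparison is confounded by effort that nobody records.

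The size is unknown from the document. If the effort raised Control attendance by 5 points, with Test at the planned 63% and 105 per area, power would fall from 90% to 71% one-sided (83% to 59% two-sided). A 10-point rise would leave 43% (31%). If it only drew in less committed registrants, the bias could run the other way. It would not follow that the primary objective cannot be answered: that would need the effort to occur and to move attendance materially, and the article establishes neither.

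**What to change.** Replace the Discussion sentence so that it agrees with Design and Setting and with the Control Area recruitment text: Control organisers keep their usual recruitment and follow-up practice and make no additional effort because of the study. Describe that usual practice briefly, since the article does not set it out and a departure can only be judged against it.

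Have each workshop in both areas keep a short dated log of promotion and reminder actions. Use it in a sensitivity analysis of the primary comparison. Start it before data collection, because it cannot be reliably rebuilt afterwards.

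Examine geographic spill-over separately, with the item already collected on how each participant learned of the workshops, and not by raising activity in Control.

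Cost: one revised sentence, a short description, an instruction to organisers and a small logging burden. No more participants are needed. The downside is that Control organisers forgo extra promotion while the study runs, which could slow recruitment of the 105 planned there.
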